### Sample size and statistical power

The RMDQ has been chosen as the primary outcome measure in keeping with prior research. Although a change of 2.5 points on the RMDQ is considered to be a minimum clinically important difference [40], prior research has based sample calculations on a between group difference of 1.8 points [4]. As the high risk intervention is the new intervention, our first hypothesis will test the superiority of ‘stratified treatment’ over previous best care for the high risk subgroup. Following statistical review of both the original STarT Back trial [10] and existing data held by the researcher (RMDQ Sd_change_ = 4.7; correlation between pre and post RMDQ ρ = 0.592), sample size calculation was performed to detect an effect size of 0.38 for the new high risk intervention over controls, with 80% power and alpha (two-tailed) = 0.05. After adjusting for ANCOVA [41], the resulting minimum sample required for each of the historical and new high risk groups is 72 patients (n = 144).

Equivalence of the stratified treatment model to standard care for medium and low risk groups will be determined if the lower boundary of the 95% CI around the mean difference RMDQ does not exceed the 1.8 threshold. For this one sided 2.5% non-inferiority hypothesis, a minimum of 57 participants in each of the medium and low risk historical and new treatment groups is necessary (n = 228). Thus, the total minimum sample is 372 patients.

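### The 72 per high-risk group appears to credit the pre-post correlation twice; with equal baseline and follow-up SDs, power is about 72–73%, not 80%

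*Protocol article*

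**What the plan says.** All the relevant text is in the protocol article under Sample size and statistical power.

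- Difference: "prior research has based sample calculations on a between group difference of 1.8 points".
- Variability: "RMDQ Sd_change_ = 4.7". No SD of the baseline or follow-up score is given.
- Correlation: "correlation between pre and post RMDQ ρ = 0.592".
- Target: "sample size calculation was performed to detect an effect size of 0.38 for the new high risk intervention over controls". The power aimed for is 80% at a two-sided 5% level.
- Result: "After adjusting for ANCOVA [41], the resulting minimum sample required for each of the historical and new high risk groups is 72 patients", or 144 in total.

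The article cites a reference for the ANCOVA adjustment but does not print the formula, and it does not say which SD standardises 0.38. The Analyses section makes the main comparison an ANCOVA with the baseline measure as covariate, so the adjustment concerns the test that will be run.

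**The concern.** Adjusting for baseline reduces the residual variance of the follow-up score by the factor 1 − ρ². A sample size may be multiplied by 1 − ρ² only if it was built on the SD of that follow-up score. A change score has already had its baseline subtracted, so its variance depends on ρ from the start. Applying 1 − ρ² to a size built on the SD of change takes credit for the same correlation a second time and makes the sample look more adequate than it is.

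The high-risk comparison is the trial's first hypothesis, and 72 per group is its stated minimum. If the residual SD is larger than the plan assumed, the chance of missing a true 1.8-point effect exceeds the declared 20%. A reader of a null result would then be relying on a power figure that the stated inputs do not support.

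**Working it through.** **Inputs**, all from Sample size and statistical power: δ = 1.8 points, SD of change = 4.7, ρ = 0.592, d = 0.38, two-sided α = 0.05, power 80%, equal groups. The one assumption added is the ratio of follow-up SD to baseline SD, which is varied in step 5.

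**1. Reproducing 72**
- 1.8/4.7 = 0.383, which matches the stated 0.38.
- A two-sample t-test at d = 0.38 needs 109.7, so 110 per group (109 by the normal approximation).
- 1 − ρ² = 1 − 0.592² = 0.6495.
- 110 × 0.6495 = 71.4, rounded up to 72. The normal route gives 109 × 0.6495 = 70.8, or 71.

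The printed figure is recovered. The residual SD it implies is 4.7 × √0.6495 = 3.79.

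**2. The factor that matches an SD of change**

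With a common SD σ at baseline and follow-up:
- Var(change) = 2σ²(1 − ρ)
- Var(ANCOVA residual) = σ²(1 − ρ²)
- Ratio = (1 − ρ²)/[2(1 − ρ)] = (1 + ρ)/2 = 1.592/2 = 0.796

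This factor does not give 72: 110 × 0.796 = 87.6.

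**3. Residual SD from the stated inputs, equal SDs**
- σ = 4.7/√(2 × 0.408) = 5.20
- Residual SD = 5.20 × √0.6495 = 4.19, against the implied 3.79

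**4. Power and size, equal SDs**

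The standard error at 72 per group is 4.19 × √(2/72) = 0.699. The effect is either 1.8 points or 0.38 × 4.7 = 1.786 points, and the two are kept apart here.

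| Effect | Power at 72: normal | t-test | ANCOVA simulation | n per group for 80% |
|---|---|---|---|---|
| 1.8 points | 73.1% | 72.5% | 71.8% | 86 |
| 1.786 points (d = 0.38) | 72.4% | 71.9% | 71.5% | 87 to 88 |

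For the first row, Φ(1.8/0.699 − 1.96) = 0.731. The required total is about 172 to 176 instead of 144.

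**5. Unequal SDs**

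Let k = baseline SD/follow-up SD. Then follow-up SD = 4.7/√(1 + k² − 2ρk), and the residual SD is that value × √0.6495. For 1.8 points, normal approximation:

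| Follow-up/baseline SD | Follow-up SD | Residual SD | Power at 72 |
|---|---|---|---|
| 0.845 | 4.70 | 3.79 | 81% |
| 0.9 | 4.90 | 3.95 | 78% |
| 1.0 | 5.20 | 4.19 | 73% |
| 1.1 | 5.43 | 4.37 | 69% |

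The first row is where the plan's factor becomes correct. If k = 2ρ = 1.184, then 1 + k² − 2ρk = 1, so the follow-up SD equals the SD of change. That requires a follow-up SD of about 4.7 and a baseline SD of about 5.6. With d = 0.38 and the t-test, power there is 80.2%, which is the plan's own claim.

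**The case against.** The best defence is that two steps are inferred. The article never writes 0.38 as 1.8/4.7 and never prints its adjustment. It says the inputs came from a review of an earlier trial and of data held by the researcher, neither of which is shown. If 0.38 was in fact standardised by a follow-up SD, then 1 − ρ² is the right factor and 72 is right. This stands as a reason for conditional wording. It does not remove the point: the only SD printed is labelled as that of change, it yields the stated effect size, and the 1 − ρ² factor recovers 72 where the matching factor does not. If 4.7 is really a follow-up SD, the label is wrong and needs correcting.

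A second objection is that a flat 73% depends on equal SDs, which the article does not give. That also stands, and the range must travel with the figure.

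Third, the shortfall neither biases the estimate nor inflates the type I error. The article names 2.5 points as the minimum clinically important difference. With a residual SD of 4.19, power for 2.5 points at 72 per group is Φ(2.5/0.699 − 1.96), about 95%. So a reader who inferred that the trial cannot detect a clinically important difference would be going beyond the document. The shortfall concerns the 1.8-point target on which the calculation was built.

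A reader might also infer that the 57 per group for the medium- and low-risk comparisons carries the same error. The document does not settle this. At d = 0.38, the 1 − ρ² factor gives 57 only from a one-sided 5% base (87 × 0.6495 = 56.5). At the stated one-sided 2.5% it gives about 71 to 72. The 57 therefore raises a question about alpha as well and should be treated separately.

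**Conclusion.** The point holds in conditional form. On the printed inputs, 72 per high-risk group appears to rest on a variance reduction that does not match the SD it was applied to. Assuming equal baseline and follow-up SDs, power is about 72–73% instead of 80%, so the risk of missing a true 1.8-point effect is about 27–28% instead of 20%. For 80%, about 86 per group (1.8 points) to 88 per group (d = 0.38) would be needed. Over follow-up/baseline SD ratios of 0.9 to 1.1, power runs from about 78% to 69%. The stated 80% is reached only if the ratio is about 0.85 or lower.

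This rests on reading 0.38 as 1.8/4.7 and the adjustment as 1 − ρ². Reproducing 72 supports both readings, but the text confirms neither. The document does not support an unqualified claim that power is 73%, because it gives no baseline or follow-up SD.

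**What to change.** Recompute the high-risk comparison with the ANCOVA residual SD and print the formula. Then do one of the following:

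- State that, with equal baseline and follow-up SDs (residual SD about 4.19), 72 per group gives about 72–73% power for the 1.8-point target. Give the range of about 78% to 69% for follow-up/baseline SD ratios of 0.9 to 1.1, and note that 80% would need about 86 to 88 per group.
- If the researcher's data show a follow-up SD near 4.7, report it together with the baseline SD, correct the label on 4.7, and keep 72.

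The cost is a few lines of text and a look at data already held. Recruitment was due to close in June 2013, before the article's publication date of December 2013, so a restated power figure is the realistic change.

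Adding archived controls to make up the shortfall should not be offered as a remedy on the present text. The article gives no count of eligible high-risk controls. The section on the best care historical control describes their outcomes at baseline and 12 weeks only, while Study design sets the primary endpoint at 6 months. It could be considered only if enough eligible high-risk controls with 6-month outcomes were shown to exist.

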#### Follow up assessment

Patients will be re-assessed at the clinic at week 12 for follow up of primary and secondary outcome measures. At 6 months, patients will be followed up by postal questionnaire. Maximising completion of follow-up questionnaires will be achieved by (1) texting the patient in advance to inform them that the questionnaire is being sent, (2) enclosing a pre-paid self addressed return envelope, (3) following up with the patient by phone once they have received the questionnaire.

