### Analyses

All data will be entered into the IBM Statistical Package for the Social Sciences [39] and subsequently cleaned and checked for normality. Baseline differences between the treatment groups will be explored with independent t tests and chi square tests. Preliminary analysis will compare pre to post intervention outcomes for each treatment group to determine if a significant treatment effect is achieved by each of the stratified interventions using paired t-tests and Cohen’s d effect size statistics. The main analysis will compare treatment response between the stratified and control groups using analysis of covariance (ANCOVA) models with baseline measures as the covariate and treatment group as the between group factor. Statistical significance will be set at p < 0.05. Missing data will be imputed using the linear and logistic regression models applied by the multiple imputation functions in SPSS and an intention to treat analysis will be performed. We will also conduct a complete case analysis for those cases where we have complete follow up data. In the event of non normal data, non parametric tests will be performed instead. Exploratory economic analyses will be undertaken. Costs of each intervention will be calculated and quality-adjusted life years (QALYs) gained computed. These will be compared between interventions using independent t tests. Six month health care utilisation attendances and associated costs will be calculated for each patient and compared between the intervention groups using chi square tests for categorical data and t tests for continuous data.

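### The 72 patients per high-risk group carry no attrition allowance, so enrolling 72 per group would give somewhat less than the stated 80% power at 6 months; 57 needs its power stated before it is relabelled

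*Protocol article*

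**What the plan says.** All sample sizes are in the article's section on sample size and statistical power. For the high-risk superiority comparison the aim is "to detect an effect size of 0.38 for the new high risk intervention over controls", "with 80% power and alpha (two-tailed) = 0.05". The only adjustment named is for ANCOVA, after which "the resulting minimum sample required for each of the historical and new high risk groups is 72 patients (n = 144" in total. The medium- and low-risk comparisons are given a margin of 1.8 RMDQ points, a one-sided 2.5% level and at least 57 per group (four groups, 228); no power is stated for them. The section concludes: "Thus, the total minimum sample is 372 patients". No attrition rate and no separate recruitment target appear anywhere in the article.

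The Study design section sets 6 months as the primary endpoint. Under Follow up assessment, "At 6 months, patients will be followed up by postal questionnaire", and three steps to improve the return rate are listed. Under Analyses, "Missing data will be imputed using the linear and logistic regression models applied by the multiple imputation functions in SPSS", within an intention-to-treat analysis, and "We will also conduct a complete case analysis for those cases where we have complete follow up data".

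**The concern.** The plan clearly expects some 6-month RMDQ scores to be missing, but the power statement is tied to a number of patients with no allowance for this. A reader would naturally take 80% as the power of the high-risk comparison once 72 patients per group are enrolled. If 72 is the zero-loss figure, that reading is too favourable: the complete-case analysis will use fewer than 72 per group, and the imputed analysis cannot fully replace scores that were never observed. The same applies to the two non-inferiority comparisons, where lost precision makes an inconclusive result more likely even if stratified care is truly no worse.

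**Working it through.** **Inputs**, all from the sample size section: effect size 0.38 (a difference of 1.8 points over an SD of 4.7 is 0.383), ρ = 0.592, two-sided α = 0.05, power 80%, 1:1 allocation. The margin for the other two strata is 1.8 points at one-sided 2.5%. The SD and the ANCOVA factor are used as the plan uses them.

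**Step 1: reproduce 72.**
- Unadjusted, normal approximation: n = 2(1.96 + 0.8416)² / 0.38² = 108.7 per group.
- ANCOVA factor: 1 − 0.592² = 0.6495.
- Adjusted: 108.7 × 0.6495 = 70.6, so 71 per group.
- With the noncentral t distribution and d = 0.38/√0.6495 = 0.4715: n = 71 gives 79.7% and n = 72 gives 80.2%.

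So 72 is the smallest number that reaches 80% with complete data. The total is the plain sum 2 × 72 + 4 × 57 = 144 + 228 = 372. Neither figure has room for loss.

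**Step 2: power of the high-risk comparison with 72 enrolled per group.** The loss rates are assumptions, because the article gives none. Imputation is given no credit here. Noncentral t, two-sided 0.05:

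| Assumed loss | Observed of 72 | Both arms lose equally | Only the new arm loses |
|---|---|---|---|
| 0% | 72 | 80.2% | 80.2% |
| 10% | 65 | 76.0% | 78.1% |
| 20% | 58 | 71.1% | 75.6% |
| 30% | 50 | 64.6% | 71.9% |

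At 5% loss in both arms the normal approximation gives 78.7%, against 80.8% at no loss on the same scale. The decline is about 2 points per 5% lost.

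**Step 3: the 57 per medium- and low-risk group.** Take the same SD and ρ and a true difference of 0.
- One-sided 2.5%, 80% power: 71 (normal) or 72 (t) per group at effect size 0.38, or 70 to 71 with 1.8/4.7. This is not 57.
- One-sided 5%, 80% power: 2(1.645 + 0.8416)² / 0.38² × 0.6495 = 55.6, so 56 (normal) or 57 (t). This matches.
- Power of 57 per group at the stated one-sided 2.5% with no loss: 70.4% with margin/SD = 0.38, 71.1% with 1.8/4.7.
- With equal loss in both groups (1.8/4.7): 66.2% with 51 observed (10%), 61.6% with 46 (20%), 55.5% with 40 (30%).

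For these strata the shortfall against 80% is there before anyone is lost; attrition adds to it.

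**The case against.** The arithmetic for 72 and for 372 is correct, and the article calls them minimum figures. It never says that enrolment stops at 372: recruitment is defined by calendar dates, and the controls come from what the Study design section describes as a large existing dataset, so the control side need not be capped at 72 or 57. If the minimum means patients available for analysis, the text is already right and lacks only a label. This stands, and it limits the point to what the number means and what power enrolment at that number would deliver.

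The size is also open to challenge. No loss rate is documented, equal loss in both arms is not established when controls are existing records, and the 12-week RMDQ gives imputation something to work with. All three are accepted: the equal-loss figures are the less favourable end, and imputation would recover part, though not all, of the loss.

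A condensed article may leave a recruitment target to the full protocol. But this article reports the whole calculation and its conclusion, so what the stated figure represents can fairly be asked.

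Two stronger readings are tempting. One is that 80% power collapses as soon as patients drop out. The figures show a gradual decline instead. The other is that all three comparisons fall below a stated 80%. The article attaches 80% only to the high-risk comparison, and attrition is not the main reason why 57 is short of it.

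**Conclusion.** The point holds in limited form. The 72 per high-risk group is the exact zero-loss result, while the plan itself provides for missing 6-month scores. If 72 per group are enrolled, power is below the stated 80% by an amount that depends on loss. Under assumed losses of 10% and 20% with no recovery through imputation, it is about 76% and 71% with equal loss, or about 78% and 76% if only the new arm loses patients. If 72 already means analysable patients, or if more are enrolled, the figure is sound and needs only its label.

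The 57 is a separate case. Assuming the same SD and ρ and a true difference of 0, it gives about 70-71% power at the stated one-sided 2.5% with full data, and reaches 80% only at one-sided 5%. Labelling it as the number of analysable patients needed would leave that mismatch standing.

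**What to change.** In the sample size section:

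1. Label 72 per group (144) as patients with an observed 6-month RMDQ.
2. Beside it, give the power expected for the numbers enrolled over a stated and justified range of 6-month loss, saying whether loss is assumed in one arm or both and whether imputation is credited. Example: with 72 enrolled per group and 20% lost in both arms, about 71% before any recovery through imputation; about 76% if only the new arm loses patients.
3. Do not base that range on the historical clinic rate alone. The description of the historical control reports monitoring at baseline and 12 weeks only, and a clinic review at 12 weeks may not predict postal return at 6 months.
4. For 57 per group, state the power at one-sided 2.5% (about 70-71% with no loss, under the assumptions above), then apply the same loss range.
5. Label the total of 372 to match, as a sum of patients with observed outcomes and not as a number that secures 80% power throughout.

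The cost is a few sentences and a less favourable power statement. No added enrolment and no change to the analysis is needed.

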### Hypotheses

The following hypotheses will be tested.

1 Patient stratified to the ‘high risk’ intervention based on the STarT Back tool will have better physical and psychological outcomes compared with their baseline scores and compared with the high risk historical control group.

2 Patients stratified to the ‘medium’ and ‘low risk’ groups based on the STarT Back tool will have significantly better physical and psychological outcomes compared with their baseline scores and equally good outcomes compared with the best-care historical control.

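### The non-inferiority rule fixes neither the direction of the RMDQ difference nor the sign of the 1.8 margin, and read literally it does not exclude worse care

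*Protocol article*

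**What the plan says.** The Hypotheses section expects medium- and low-risk patients to have "equally good outcomes compared with the best-care historical control". The section on sample size and power turns this into a decision rule: equivalence is concluded if "the lower boundary of the 95% CI around the mean difference RMDQ does not exceed the 1.8 threshold". The next sentence labels the test and gives its size: "For this one sided 2.5% non-inferiority hypothesis", at least 57 patients are needed in each of four groups (228 of the planned 372).

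The figure of 1.8 comes from the same section, where "prior research has based sample calculations on a between group difference of 1.8 points"; the section also gives 2.5 points as the minimum clinically important change. The planning inputs are "RMDQ Sd_change_ = 4.7; correlation between pre and post RMDQ ρ = 0.592".

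The between-group difference is to come from "analysis of covariance (ANCOVA) models with baseline measures as the covariate and treatment group as the between group factor" (Analyses). That model is unobjectionable. However, neither it nor any other passage says whether the difference is stratified minus control or the reverse, or whether it is in scores or in improvement.

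**The concern.** The RMDQ measures disability, so a higher score is a worse result. A non-inferiority rule must require the confidence limit on the harmful side to stay inside the margin. Which limit that is, and whether the margin is +1.8 or -1.8, depends on how the difference is formed.

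The written rule leaves this open and then states an inequality that works in neither case:

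- **Stratified minus control score (positive is harm).** The upper limit should be below +1.8. Requiring only that the lower limit not exceed +1.8 fails the new care only when it is significantly worse than the margin.
- **Benefit difference (positive favours stratified care).** The lower limit is the right one, but it should be above -1.8. Requiring it not to exceed +1.8 passes every harmful result and fails only a large benefit.

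The rule decides the between-group part of the second hypothesis in two of the three strata. It matters most for low-risk patients, who attend a single 1.5-hour session, whereas the controls had four weekly 1.5-hour classes followed by eight weeks of structured home exercise. A literal application would treat a lack of proof of harm as proof that there is none.

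**Working it through.** **Inputs** (Sample size and statistical power): SD of change 4.7; pre-post correlation 0.592; margin 1.8; 57 per group. The superiority calculation is "to detect an effect size of 0.38 for the new high risk intervention over controls, with 80% power and alpha (two-tailed) = 0.05". Two assumptions are needed: the ANCOVA adjustment multiplies n by 1 - ρ², and the 80% power carries over to the non-inferiority part, where power is not restated.

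**The plan's own sample sizes.** 1 - 0.592² = 0.6495.

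- Superiority: effect size 0.38, two-sided 5%, 80% power gives 110 per group (t-based). 110 × 0.6495 = 71.4, so 72. This reproduces.
- Non-inferiority: at the stated one-sided 2.5% the same route gives 70 to 72, not 57. At one-sided 5% it gives 87 × 0.6495 = 56.5, so 57.

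The mismatch in the second figure is a separate matter. Here 57 serves only as the planned group size.

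**Standard error.** SE = SD × √(2/57).

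- Factor applied to the SD of change: 4.7 × √0.6495 = 3.79; SE = 0.710; half-width 1.96 × 0.710 = 1.39.
- Via the raw-score SD, assuming equal variances before and after: 4.7 / √(2 × (1 - 0.592)) = 5.20; 5.20 × √0.6495 = 4.19; SE = 0.785; half-width 1.54.

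**Literal rule, stratified minus control score.** It passes if observed difference - half-width ≤ 1.8.

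- Largest passing disadvantage: 1.8 + 1.39 = 3.19, or 1.8 + 1.54 = 3.34.
- Pass rate at a true disadvantage δ: Φ((1.8 + 1.96·SE - δ)/SE). At δ = 1.8 this is Φ(1.96) = 97.5%. At δ = 2.5 it is 83.5% (SE 0.710) or 85.7% (SE 0.785).

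**Valid rule, score difference.** It passes if observed difference + half-width < 1.8.

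- Largest passing disadvantage: 1.8 - 1.39 = 0.41, or 1.8 - 1.54 = 0.26.
- Pass rate: Φ((1.8 - 1.96·SE - δ)/SE), which is 2.5% at δ = 1.8 and 0.2% at δ = 2.5.

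**Comparison of readings** (SD 3.79; SD 4.19 in brackets where it differs)

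| Difference and rule | Observed results that pass | Truly 1.8 worse | Truly 2.5 worse |
|---|---|---|---|
| Score difference, lower limit ≤ +1.8 (literal) | disadvantage up to 3.19 (3.34) | 97.5% | 83.5% (85.7%) |
| Benefit difference, lower limit ≤ +1.8 (literal) | any disadvantage, and benefit up to 3.19 (3.34) | about 100% | about 100% |
| Score difference, upper limit < +1.8, or benefit difference, lower limit > -1.8 | disadvantage below 0.41 (0.26) | 2.5% | 0.2% |

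Only the last row agrees with a one-sided 2.5% non-inferiority test.

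**The case against.** The strongest reply is that the authors meant a valid rule and worded it loosely. The Outcome measures section describes the primary outcome as change in disability, the Analyses section speaks of treatment response, and the sample size uses the SD of change. On an improvement scale the lower limit is the correct one. Not exceeding 1.8 can then mean not going beyond 1.8 points in the harmful direction, and the one-sided 2.5% label in the next sentence fits that reading.

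Much of this stands. A reader might infer that the plan uses the wrong confidence limit and so will declare clearly worse care equivalent. The document does not support that, because it never fixes the direction of the difference. On a benefit scale only the sign and the inequality are wrong, and the pass rates of 97.5% and 84 to 86% do not apply.

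It does not rescue the sentence. The benign reading has to supply a benefit-direction difference and a minus sign, and the text has neither. Change taken as follow-up minus baseline still has higher values worse, so the word alone does not settle the direction. Nor is this a detail left to an unseen analysis plan: the protocol states the rule and its threshold itself.

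The complaint about the word equivalence is secondary, since the next sentence names the test as one-sided non-inferiority.

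**Conclusion.** The rule is invalid as written. Direction and sign are undefined, and its literal form does not rule out worse care under either order of subtraction, which conflicts with the stated one-sided 2.5% test.

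The size is conditional. For stratified minus control scores with the inequality taken literally, 57 per group and a residual SD of 3.79 to 4.19, an observed disadvantage of up to about 3.2 to 3.3 points passes. That is beyond the 2.5 points the plan cites as clinically important. The pass rate is 97.5% at a true 1.8 points worse and about 84 to 86% at 2.5 points worse. The SD of 4.19 rests on equal variances before and after treatment.

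That the authors intended, or would apply, the harmful version is not shown. What is shown is that the criterion for two of the three strata cannot be applied safely as it stands.

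**What to change.** Define the difference and restate the rule, for example:

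> Non-inferiority in a stratum is concluded if the upper limit of the two-sided 95% CI for the baseline-adjusted mean difference in RMDQ (stratified minus control; higher = worse) is below +1.8.

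The equivalent form on a benefit scale is that the lower limit of the benefit difference is above -1.8. State one of them and use it throughout. Describe the conclusion for the medium- and low-risk groups as non-inferior in both the Hypotheses and the sample size sections.

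The cost is one sentence and a few words, with no extra data. The direction should be fixed before the outcome comparison is seen. The change does not settle whether 57 per group is enough at one-sided 2.5%, which needs its own check.

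### On the inputs printed, the one-sided 2.5% non-inferiority comparisons need about 72 patients per group for 80% power; the stated 57 gives about 71%

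*Protocol article*

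**What the plan says.** All the figures are in the protocol article, section Sample size and statistical power.

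- **High risk, superiority.** The inputs are "RMDQ Sd_change_ = 4.7; correlation between pre and post RMDQ ρ = 0.592". The target is an effect size of 0.38 for the new programme against its control, and the error rates are given as "with 80% power and alpha (two-tailed) = 0.05". The ANCOVA adjustment then brings this to 72 per group, 144 in all.
- **Medium and low risk, non-inferiority.** The stratified model is accepted "if the lower boundary of the 95% CI around the mean difference RMDQ does not exceed the 1.8 threshold". The size follows: "For this one sided 2.5% non-inferiority hypothesis, a minimum of 57 participants in each of the medium and low risk" groups, both historical and new, 228 in all.
- **Total.** "Thus, the total minimum sample is 372 patients".

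The non-inferiority paragraph restates no SD, correlation or power. The section Hypotheses expects outcomes in these two strata to be as good as in the historical control, which corresponds to a true difference of zero.

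**The concern.** A one-sided 2.5% test and a two-sided 5% test use the same critical value, 1.96. The superiority effect size of 0.38 is 1.8/4.7, so it stands for the same 1.8 points that serve as the non-inferiority margin. With a true difference of zero, the distance to be resolved is identical in the two calculations. With the same SD, correlation and power the two sample sizes should therefore agree, yet the section gives 72 for one and 57 for the other.

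The medium- and low-risk comparisons with the historical control are the between-group part of the second hypothesis. If they are smaller than their stated error rates require, a confidence interval that fails the 1.8 criterion could reflect the shortfall and not worse care. The figure also carries into the overall total.

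**Working it through.** **Inputs** (all from Sample size and statistical power, except the last):
- margin 1.8 points; SD of change 4.7; 1.8/4.7 = 0.383, printed as 0.38
- ρ = 0.592, so the ANCOVA factor is 1 − 0.592² = 0.6495
- power 80%, stated once, with the superiority calculation
- equal group sizes
- true difference 0 under non-inferiority: an assumption, in line with the second hypothesis

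**Formula.** Per group, n = 2(z₁₋α + z₁₋β)² / d² × (1 − ρ²), with α one-sided. The t-test version replaces the first factor with the t-test sample size, rounded up before the ANCOVA factor is applied.

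**Step 1: reproduce the plan's 72.** Two-sided 5%, 80% power, d = 0.38: the t-test needs 109.7, rounded up to 110. Then 110 × 0.6495 = 71.4, rounded up to **72**. This matches, so the method is identified.

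**Step 2: same method for non-inferiority at one-sided 2.5%, 80% power.** The critical value and the distance are unchanged, so the result is again **72**. Variants:

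| d | Normal approximation | t-test |
|---|---|---|
| 0.38 | 70.6 → 71 | 110 × 0.6495 = 71.4 → 72 |
| 0.383 | 69.5 → 70 | 108 × 0.6495 = 70.1 → 71 |

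The range is 70 to 72. None gives 57.

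**Step 3: what does give 57.** With d = 0.38 and the method of Step 1:
- one-sided 5%, 80% power: 86.3 → 87; 87 × 0.6495 = 56.5 → **57**
- one-sided 2.5%, 70% power: 86.5 → 87; 87 × 0.6495 = 56.5 → **57**

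The two routes share the same intermediate figures, so the match cannot tell them apart.

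**Step 4: other readings at 2.5% and 80%.**
- No ANCOVA adjustment: 108.
- Two one-sided tests for equivalence, with ANCOVA: about 93 to 95.
- Margin of 2.5: 56 without ANCOVA and 37 with it, but the stated margin is 1.8.
- Keeping ρ = 0.592, 57 would need an SD of change of about 4.26. Keeping the SD at 4.7, it would need ρ of about 0.68 to 0.69. Neither is stated.

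**Step 5: power with 57 per group at one-sided 2.5%.** Standardised distance after ANCOVA: 0.38/√0.6495 = 0.4715. Then 0.4715 × √(57/2) = 2.517; 2.517 − 1.960 = 0.557; Φ(0.557) = 0.711.

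| d | Normal approximation | t-test |
|---|---|---|
| 0.38 | 0.711 | 0.704 |
| 0.383 | 0.718 | 0.711 |

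For comparison, 72 per group with d = 0.38 gives 0.808 (normal) or 0.802 (t).

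**Step 6: totals.** As stated: 4 × 57 = 228, and 144 + 228 = 372. At 72: 4 × 72 = 288, and 144 + 288 = 432.

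**The case against.** The non-inferiority paragraph gives no SD, correlation or power, so 72 follows only if the values printed for the high-risk calculation carry over. A condensed article may leave stratum-specific inputs to a fuller document, and a somewhat smaller SD in the milder strata would justify 57. This stands as a limit on the claim: 57 does not follow from the inputs shown, but it is not shown to be wrong under every possible input. It does not rescue the text, because a reader has only one set of inputs and they contradict the number.

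A reader might infer that 57 was computed at one-sided 5%, that is, for a 90% confidence interval. The exact match makes this likely, but the documents do not establish it. The text says 2.5% and 95% CI, which agree with each other, and 2.5% with 70% power gives the same 57. The match also needs the rounded 0.38; with 0.383 the 5% calculation gives 56. That is a minor point, since 0.38 is the printed effect size and is also what yields 72.

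A reader might also add a further power loss by asking whether the ANCOVA factor belongs on an SD of change. That is a separate question. It needs an added assumption about the baseline and follow-up SDs, and it would affect the 72 equally.

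Finally, the decision rule itself is unaffected. A shortfall makes non-inferiority harder to claim and does not raise the type I error rate.

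**Conclusion.** The point holds: the stated 57 per group is inconsistent with the stated test. On the margin, SD, correlation and power printed in the section, with equal groups and a true difference of zero, the requirement is about 72 per group (70 to 72). At one-sided 2.5%, 57 per group gives about 70 to 71% power by the t-test (up to 72% by the normal approximation), not 80%. The chance of missing true non-inferiority is then 28 to 30% in each of the two strata. If 70% power was in fact intended, the size is the same but the article does not disclose it. The cause remains open. The conclusion would change only if different inputs were used for these strata, and none are given.

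**What to change.** Keep the 95% CI, one-sided 2.5% rule, and do not bring it into line with 57 by moving to a 90% interval. Then restate the size in one of two ways:

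- keep 57 per group and report its actual power at one-sided 2.5%, about 71% on the stated inputs; the total stays at 372, described as giving that power in the medium- and low-risk strata; or
- state 72 per group as the number required for 80% power, with 288 for the four groups and a total of 432.

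If a different SD, correlation or power was used for the medium- and low-risk strata, print it beside the 57.

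The cost is one or two sentences. The Conclusions section has recruitment closing in June 2013, so the first option is the practical one; it needs no extra patients.
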